### Interventions

2.4

Each acupuncture treatment modality will involve three sessions, each lasting 30 min, administered over two consecutive days (first hour, first day, second day after delivery). This intensive regimen (three sessions within 48 h postpartum) was chosen because the initial 6–12 h postpartum represent the critical window for the onset of PUR. The goal is to provide repeated neuromodulatory stimulation during this period to maximize preventive effects on bladder recovery. The selection of acupuncture points is based on traditional Chinese medicine theory, evidence-based clinical research, and our accumulated clinical experience. The treatment protocol adheres to CONSORT and STRICTA recommendations, providing comprehensive details on the treatment, including the number of needles used, session frequency, and treatment duration. Only licensed acupuncturists holding a master’s degree and possessing more than 2 years of acupuncture experience will conduct the treatment. Prior to the study commencement, all acupuncturists at each sub-center will receive instruction in the theory of PUR and standardized operating procedures.

#### Electro-acupuncture group

2.4.1

The selected acupoints will include Baihui (GV20), Zhongji (CV3), and Guanyuan (CV4), adhering strictly to the National Acupoint Standard of the People’s Republic of China in 2021 (GB/T 12346–2021). The first treatment session will be initiated within 1 h postpartum (±30 min). Detailed positioning is illustrated in Table 2 and Figure 2. Patients will be positioned supine during the procedure. Adhesive pads will be applied to the skin over the acupoints, followed by the insertion of single-use acupuncture needles (0.25 mm * 40 mm, Hwato, Suzhou, China) through the adhesive pads.

**Table 2 tab2:** Locations and needling methods of acupoints for electro-acupuncture group.

Acupoint	Location	Needling method
Baihui (GV20)	On the head, 5 inches above the center of the front hairline.	Depth of 10-15 mm and an angle parallel to the scalp, then adopt the method of small amplitude and high frequency twisting(the range of twirling of the needle was 90°- 180°, and the frequency was 100 to 120 times a minute) for 1 min.
Zhongji (CV3)	In the lower abdomen, 4 cun below the umbilicus, on the anterior median line.	Obliquely acupunctured 10-20 mm and at a 45° angle to the abdomen.
Guanyuan (CV4)	In the lower abdomen, 3 cun below the umbilicus, on the anterior median line.	Obliquely acupunctured 10-20 mm and at a 45° angle to the abdomen.

**Figure 2 fig2:**
[figure not shown]
**(A)** Shows the specific location of the two groups of acupoints; **(B)** Shows the connection method of the EA apparatus; **(C)** Shows active acupuncture and sham acupuncture.

The sequence and technique of acupuncture are as follows: GV20 will be needled at a depth of 10–15 mm with an angle parallel to the scalp, followed by small-amplitude, high-frequency twirling (90°–180°, 100–120 rotations/min for 1 min). CV3 and CV4 will then be obliquely punctured at 10–20 mm with a 45° abdominal angle and manipulated with the same twirling parameters for 1 min. Practitioners will apply standardized manual stimulation per STRICTA to elicit characteristic needling sensations (e.g., aching, heaviness, distension)—terms traditionally referred to as “de qi”; this terminology is used in its historical context and does not imply a validated biomedical mechanism. To operationalize sensation intensity, participants will rate needling sensations using a 0–10 Numeric Rating Scale (0 = no sensation, 10 = strongest imaginable sensation) immediately after needle manipulation, and practitioners will record perceived needle grasp (present/absent). Paired electrodes from an EA device (SDZ-IIB, Suzhou Medical Appliance) will be attached to the CV3 and CV4 needles, set to continuous 2 Hz, with current intensity adjusted individually between 1 and 5 mA to produce visible, comfortable local muscle twitching without pain. Needles will be retained for 30 min. The procedure and electrode connections are shown in Figure 2.

#### Sham acupuncture group

2.4.2

Patients in the sham group will receive a non-insertive procedure matched to the EA group for time, attention, body position, and device appearance. Stimulation will be delivered at three predefined non-acupoint sites labeled sham-Baihui, sham-Zhongji, and sham-Guanyuan. Blunt-tip telescopic sham needles (0.25 mm× 40 mm, Hwato, Suzhou, China) will rest on the skin through adhesive guide tubes without skin penetration; no manual twirling will be performed and practitioners will not aim to elicit characteristic needling sensations (traditionally termed “de qi”). Leads from an EA device (SDZ-IIB, Suzhou Medical Appliance, Suzhou, China) will be attached to the sham-Zhongji and sham-Guanyuan simulators with the device powered on but current set to 0 mA (no output). The simulators will remain in place for 30 min, with the number and schedule of sessions identical to the EA group. Specific procedures are summarized in Table 3 and Figure 2.

**Table 3 tab3:** Locations and needling methods of non-acupoints for Sham group.

Acupoint	Location	Needling method
Sham-Baihui	2 cun lateral from GV20	Sham needles will not penetrate the skin
Sham-Zhongji	6 cun lateral from CV4(left)	Sham needles will not penetrate the skin
Sham-Guanyuan	6 cun lateral from CV4(right)	Sham needles will not penetrate the skin

### Outcome measurements

2.5

At the baseline, clinical and sociodemographic data will be collected from all patients, encompassing:(1) Basic Information:Age;Gestational age at delivery;Height;Weight (Predelivery);Body Mass Index (Predelivery);Conception mode.(2) Management of the Delivery Process:Duration of labor;Use of epidural anesthesia;Incidence of episiotomy and perineal lacerations;Instances of vacuum-assisted and instrumental delivery;Process of placental delivery;Administration of uterine contractile drugs.(3) Newborn Condition:Weight;Length;Apgar score.

#### Primary outcome

2.5.1

The primary outcome is the PUR incidence.

The incidence of postpartum urinary retention (PUR) will be evaluated in accordance with the following criteria, which are grounded in the diagnostic guidelines outlined in “Postpartum urinary retention: an expert review” published in the American Journal of Obstetrics and Gynecology.Overt PUR: Inability to void spontaneously within 6 h postpartum or within 6 h after removal of the indwelling catheter following cesarean section.Covert PUR: Post-void residual (PVR) urine volume ≥ 150 mL after spontaneous voiding.Persistent PUR: Requirement for an indwelling catheter or intermittent catheterization by the 3rd day postpartum.

Assessment time points are: the first urination after delivery, 6 h after delivery, the initial urination on the first day, and the second day following acupuncture. Meeting any of the aforementioned criteria at any assessment point will be considered as a positive PUR case.

The PVR of the bladder will be measured using an Ultrasonic Bladder Scanner (BVI-9400 BladderScan^®^, Verathon Medical Europe, Ijsselstein, The Netherlands). All BladderScan BVI-9400 devices will be calibrated annually according to the manufacturer’s guidelines. Operators must complete a standardized training program and pass a competency assessment before performing study measurements. To ensure accuracy, any PVR measurement ≥150 mL will be immediately rechecked by a second, blinded operator within 15 min. The average of the two readings will be recorded as the final PVR value. The recorded PVR of the bladder and whether catheterization was required will be documented. The specific measurement times are illustrated in Figure 3.

**Figure 3 fig3:**
[figure not shown]
Intervention time nodes chart.

#### Secondary outcome

2.5.2

##### The time of first urination, the amount of urination and the feeling of unobstructed urination

2.5.2.1

(1) Recording time from delivery completion to first urination:

The elapsed time from the conclusion of delivery to the initiation of the first urination will be recorded, measured in minutes (“min”).(2) Recording volume of first post-delivery urination:

After urination in a urinal, the volume of urine will be measured using a cup, expressed in milliliters (“mL”).(3) Assessment of unobstructed feeling during first urination:

The unobstructed sensation during the initial urination will be evaluated using the Traditional Chinese Medicine Syndrome Quantification Scale, where:0 points: Unable to urinate;2 points: Dribbling out urine, with a sense of difficulty;4 points: Urination is acceptable, with a residual feeling;6 points: Very smooth, without any residual sensation.

##### Effective rate of urination

2.5.2.2

The classification of the first urination volume is as follows:A volume greater than 500 mL is considered significant;A volume ranging from 100 to 500 mL is deemed effective;A volume less than 100 mL is categorized as invalid.

The effective rate of urination is calculated using the formula: Effective rate of urination = (number of significant cases + number of effective cases)/total cases × 100%.

##### Postpartum uterine contraction pain

2.5.2.3

The Visual Analogue Scale (VAS) will be employed to assess postpartum uterine contraction pain. The visual scale spans 10 centimeters, ranging from 0 to 10, where “0” represents a painless state, and “10” signifies the most unbearable pain. Scores will be assigned at specific time points, including 6 h after delivery, 2 h after acupuncture on the first day, and 2 h after acupuncture on the second day.

##### Cumulative amount of 24 h postpartum bleeding

2.5.2.4

The volume of vaginal bleeding within the first 24 h after delivery will be documented using postpartum measuring pads. These pads will be changed regularly every 2–4 h, and upon replacement, they will be weighed and measured, with the unit of measurement being milliliters (“mL”). Blood loss will be measured using pre-weighed pads changed every 2–4 h, with volume (mL) calculated as weight difference (g) × 1.06 (density conversion factor). Permitted co-interventions include uterotonics (e.g., oxytocin) but exclude prophylactic catheterization. All co-interventions will be recorded and adjusted for in the analyses.

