### Statistical analysis

2.10

Demographic characteristics, general situations, and baseline conditions of the two groups will be compared and analyzed. For measurement data, an independent samples t-test or Wilcoxon rank-sum test will be employed, while χ^2^ test or Fisher test will be used for categorical data.

The incidence of PUR will be accurately assessed using Fisher’s exact test, and the relative risk (RR) along with the corresponding 95% confidence interval will be calculated. For other ordinal data, the Wilcoxon rank-sum test will be applied, while clinical counting data will undergo testing through the χ2 test. Postpartum depression and anxiety will be compared using Fisher’s exact test, and the RR along with the corresponding 95% confidence interval will be computed. Subject blinding effectiveness will be analyzed using the James Blinding Index. All statistical tests will be two-sided, and a *p* value less than 0.05 will be considered statistically significant for the tested differences.

For exploratory subgroup analysis, participants will be stratified into different subgroups based on age (< 40 years, ≥ 40 years), BMI (< 25 kg/m^2^, ≥ 25 kg/m^2^), duration of labor (< 700 min, ≥ 700 min), epidural anesthesia (with or without), vaginal midwifery techniques (forceps midwifery, fetal head attraction midwifery, fetal head rotation, perineotomy), gestational age (> 280 days, ≤ 280 days), and newborn birth weight (< 4,000 g, ≥ 4,000 g). The incidence difference between the two groups will be compared within each subgroup using the same statistical methods as mentioned above.

The primary analysis will follow the intention-to-treat (ITT) principle. Missing data will be handled using multiple imputation. A logistic regression model adjusting for study center will be used for the primary outcome. Secondary and subgroup analyses will apply Bonferroni correction for multiple comparisons.

GraphPad Prism 10.2 will be used for all statistical analysis.

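### Pad weight is multiplied by a blood density of 1.06 when it should be divided, so every 24-hour blood-loss value derived as written is about 12% too high

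*Protocol article*

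**What the plan says.** Twenty-four-hour blood loss is a secondary outcome with its own section, 2.5.2.4, and its own row in Table 1. The section defines the outcome as a volume: "The volume of vaginal bleeding within the first 24 h after delivery will be documented using postpartum measuring pads". The raw measurement is a mass: "Blood loss will be measured using pre-weighed pads changed every 2–4 h". The conversion from one to the other is given in the same sentence: "with volume (mL) calculated as weight difference (g) × 1.06 (density conversion factor").

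No other part of the article gives a different formula, and no unit is printed for 1.06. For continuous data, section 2.10 says: "For measurement data, an independent samples t-test or Wilcoxon rank-sum test will be employed". That sentence follows the one on baseline comparisons, but it is the only test the article names for measurement data. Section 2.5.2.4 adds that co-interventions will be adjusted for.

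**The concern.** The article calls 1.06 a density conversion factor. If a fluid has a density of 1.06 g/mL, each millilitre weighs 1.06 g, so a given weight in grams corresponds to a smaller number of millilitres. The printed rule gives a larger number. The correction is therefore applied in the wrong direction, and treating grams as millilitres with no correction at all would be nearer the truth.

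The error is systematic. It would affect every participant at every centre, so neither randomization nor sample size removes it. Monitoring against the protocol would confirm the wrong values as correct. A reader of the eventual results table could not detect it, and the reported millilitres could not properly be compared, or pooled as mean differences, with those of studies that converted correctly.

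**Working it through.** **Inputs, all from section 2.5.2.4**

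- Measured quantity: weight gain W of the pads, in g.
- Reported quantity: volume V, in mL.
- Factor: 1.06, described as a density. The unit g/mL is an assumption that follows from that description.

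**The two rules**

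- As printed: V = W × 1.06.
- From the definition density = mass / volume: V = W / 1.06.

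**Ratio of printed to correct value**

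(W × 1.06) / (W / 1.06) = 1.06² = 1.1236, an overstatement of 12.36% at every weight. The rule is linear, so it makes no difference whether the conversion is applied pad by pad or to the 24-hour total.

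| Weight gain (g) | Printed rule (mL) | Divided by 1.06 (mL) | Excess (mL) |
|---|---|---|---|
| 100 | 106.0 | 94.3 | 11.7 |
| 300 | 318.0 | 283.0 | 35.0 |
| 500 | 530.0 | 471.7 | 58.3 |

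Against the raw gram figure, the printed rule adds 6.0%. The density correction should subtract 1 − 1/1.06 = 5.7%.

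**Could the multiplication be right under another reading?** It would be dimensionally valid if 1.06 were a specific volume in mL/g. That contradicts the word density, and it implies a fluid of 1/1.06 = 0.943 g/mL, lighter than water. This reading fails.

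**What carries through to the analysis**

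- The error is one constant multiplier in both arms. Means, standard deviations, the difference in means and any covariate-adjusted difference in mL are all multiplied by 1.1236.
- Ratios of means, standardized differences, and t-test and Wilcoxon p-values do not change. This was checked on simulated skewed data with 330 per arm. The t-test p-value (5.06 × 10⁻⁶) and the rank-sum p-value (2.31 × 10⁻⁶) were the same under both rules, while the mean difference moved from −49.9 to −56.0 mL, and 56.036 / 49.872 = 1.1236.
- A count of women above a fixed volume would shift. For example, a recorded 500 mL would correspond to 500 / 1.1236 = 445.0 mL. The article sets no blood-loss cut-off for this outcome, so this matters only if one is applied later.

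**The case against.** The best case on the other side accepts that the formula is inverted and argues that little follows from it.

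- **Limited reach.** Blood loss is one of several secondary outcomes. The primary outcome and the sample size rest on the incidence of urinary retention and use no blood-loss figure. A multiplier common to both arms creates no bias in the comparison and cannot change a significance test. This stands.
- **Reversible.** If the printed rule was followed everywhere, dividing the stored volumes by 1.1236 recovers the correct values. This stands, but only on that condition. If some centres multiplied and others divided, there would be a 12.4% discrepancy between centres that no single rescaling could repair. Only the raw weights would resolve it.
- **No threshold in the plan.** The article mentions postpartum hemorrhage in sections 2.2.4 and 2.5.3, but ties neither mention to a pad-derived volume. This stands, so no claim is made here that participants would be misclassified under the plan as written.
- **Possibly a drafting slip.** The database may already divide. The article does not say where the conversion is done, so this cannot be excluded. It does not excuse the text: the sentence is complete, the multiplication sign is explicit, and this is the rule that sites and data checkers would follow.

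These points limit the damage. None of them makes the formula right.

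**Conclusion.** The conversion rule is wrong as written. If it is applied as printed, every 24-hour blood-loss value is overstated by a factor of 1.1236 (12.4%), as are the arm means, standard deviations and the between-group difference in mL.

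Two assumptions are needed: that 1.06 is in g/mL, and that sites or the database follow the printed sentence. The first is close to certain from the article's own label. The second cannot be verified from the article. The consequence is a wrong absolute scale for one secondary outcome. The hypothesis test for that outcome, its ratio of means, the primary outcome and the sample size are unaffected.

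**What to change.** In section 2.5.2.4, replace the rule with: volume (mL) = weight difference (g) / 1.06 (g/mL), with the unit printed. Make the same change wherever the conversion is carried out, whether in the electronic CRF, on a site worksheet or in the analysis program. Keep the raw pad weights in the database.

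Before database lock, ask each centre which operation it has actually used, and re-derive all volumes already entered from the weights. If only volumes were stored and a centre is confirmed to have multiplied, divide that centre's values by 1.1236.

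The cost is one line in the protocol, one derivation and a short query to four centres. No new data collection is needed if the weights were kept, and no other outcome is affected.

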#### Drop-out and discontinuation criteria

2.2.4

All randomized participants will be included in the Intention-to-Treat (ITT) analysis. The Full Analysis Set (FAS) will be identical to the ITT population. Participants who meet any of the following protocol deviation criteria will be excluded from the Per-Protocol (PP) analysis but retained in the ITT/FAS. All participants who receive at least one session of acupuncture (active or sham) will be included in the Safety Analysis Set. Sensitivity analyses will be conducted to explore the impact of major protocol deviations.Rescue measures are implemented due to postpartum hemorrhage, eclampsia, or other obstetric conditions;Conversion from vaginal delivery to cesarean section.Infection is diagnosed during delivery;An indwelling catheter is used and diuretics are administered due to other diseases within 6 h after delivery;A degree III laceration above the perineal fissure is diagnosed;Due to other postpartum reasons, the number of treatment sessions received by patients is less than 3 times, which affects the analysis and judgment of the results;The researchers can terminate the patients from the study at any stage if any events occur that may affect the safety of patients in the study.

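### The rule to adjust for every co-intervention is not limited to those given before treatment, so it can condition on effects of electroacupuncture, and it does not match the centre-only primary model

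*Protocol article*

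**What the plan says.** Section 2.5.2.4 defines the bleeding outcome: "The volume of vaginal bleeding within the first 24 h after delivery will be documented using postpartum measuring pads". It then states which co-interventions are allowed, "Permitted co-interventions include uterotonics (e.g., oxytocin) but exclude prophylactic catheterization", and closes with the rule at issue: "All co-interventions will be recorded and adjusted for in the analyses". The rule carries no limit by timing, indication, outcome, or role of the analysis.

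The timing of treatment comes from sections 2.4 and 2.4.1. Three sessions are "administered over two consecutive days (first hour, first day, second day after delivery"), and for the first of them the text reads "The first treatment session will be initiated within 1 h postpartum (±30 min").

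Section 2.10 sets the primary analysis as intention-to-treat and gives its model: "A logistic regression model adjusting for study center will be used for the primary outcome". It names no co-intervention. For the secondary outcomes it lists tests without covariates.

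Two other places bear on the point. Section 2.5 lists "Administration of uterine contractile drugs" among the baseline data on management of the delivery. Section 2.2.4 removes from the per-protocol set, but keeps in the ITT set, women for whom "Rescue measures are implemented due to postpartum hemorrhage, eclampsia, or other obstetric conditions".

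**The concern.** Randomisation protects a comparison adjusted for variables fixed before treatment. It does not protect one adjusted for variables that treatment can change. A uterotonic given some hours after the first session acts on uterine tone and bleeding and may be prompted by them. The Discussion names contraction pain and bleeding as outcomes on which EA's influence will be explored. If EA reduces early bleeding and so reduces later uterotonic use, a model holding uterotonic use constant removes part of the effect it should measure. If an unmeasured factor also drives both uterotonic use and the outcome, the adjustment can create an association where there is none. A larger sample removes neither problem.

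The second issue is consistency. The same article adjusts for all co-interventions in one section and for centre alone in another. Left as it is, the covariate set can be argued either way after the data are seen.

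**Working it through.** The plan gives no figure to reproduce here, so the check has two parts: the timing read from the text, and simulations that show direction only.

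**1. Timing.** Bleeding is measured over 0 to 24 h. Session 1 is at about 1 h with a 30 min tolerance, so at the latest about 1.5 h. Of the outcome window, 24 − 1 = 23 h (at least 24 − 1.5 = 22.5 h) follows the start of treatment. This is a share of time, not of blood lost, which the document does not give. Contraction pain (2.5.2.3) is scored at 6 h and 2 h after acupuncture on each of the first and second days, so every score follows session 1. Co-interventions recorded over these windows can therefore come after treatment.

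**2. The two rules side by side.**

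| Section | Scope | Covariates |
|---|---|---|
| 2.5.2.4 | the analyses, unspecified | all co-interventions |
| 2.10 | primary outcome | study centre |

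Both cannot describe the same primary model.

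**3. Bleeding, assumed inputs, set A.** Let *a* be arm, and *u*, *e1*, *e2*, *e3* independent standard normals.
- Early loss = 200 + 60*u* + 40*e1* + *t·a*, where *t* is the assumed EA effect in mL.
- Post-treatment uterotonic given if early loss + 30*e2* > 260 (about 22% of controls).
- Late loss = 100 + 30*u* + 20*e3* − 20 if a uterotonic is given.
- Outcome = early + late, fitted by least squares on arm, without and with the uterotonic indicator.

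| Uterotonic | *t* | Unadjusted (mL) | Adjusted (mL) | Removed |
|---|---|---|---|---|
| after session 1 | −20 | −18.6 | −9.1 | 1 − 9.1/18.6 = 51% |
| after session 1 | −40 | −37.5 | −20.4 | 1 − 20.4/37.5 = 46% |
| after session 1 | 0 | about 0 | about 0 | none |
| before session 1 | −20 | −19.5 | −19.6 | none |
| before session 1 | −40 | −40.1 | −40.0 | none |

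**4. Bleeding, assumed inputs, set B.** Early loss is gamma with mean 250 and SD 100, less 30 mL under EA. A uterotonic is given if early loss plus noise exceeds 280 to 350 mL. Total loss adds N(100, 50), less 0 or 60 mL if treated. Varying the noise SD from 0 to 150 mL moved the attenuation from 7% to 53%. With no EA effect, adjusted estimates were again about 0.

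**5. PUR, no true effect, assumed inputs.** EA lowers co-intervention use from 34% to 21%, and an unmeasured factor raises both that use and PUR. The crude odds ratio is 1.00 and the ratio stratified on the co-intervention is 1.12. If EA does not affect co-intervention use, the stratified ratio is 1.00.

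**The case against.** The strongest reply is that the harmful reading is inferred. Section 2.5.2.4 does not say when or why uterotonics are given. The only other mention of such drugs, in section 2.5, places them with the delivery data. If that is the variable meant, it largely precedes session 1 and adjusting for it is harmless, as the lower rows of the table show. This stands as a possible reading. But the rule says all, and nothing confines it to delivery drugs.

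Second, the sentence sits in one secondary-outcome subsection, while section 2.10 specifies the primary model. A reader might infer that the PUR comparison itself will be biased. The document does not support that: the specific statement in 2.10 plausibly governs PUR, and the 1.12 above needs an adjusted PUR model, an EA effect on co-intervention use, and an unmeasured common cause. A reader might also infer that PUR would be adjusted for catheterization, which is part of the persistent PUR definition. The article excludes prophylactic catheterization and documents the need for a catheter with the primary outcome; it nowhere calls therapeutic catheterization a co-intervention.

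Third, 2.10 gives no adjusted model for secondary outcomes, and covariate definitions may be left to an analysis plan not shown. That is fair as to detail. The sentence is nonetheless an affirmative commitment, and a later plan that follows it would inherit the problem.

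Fourth, one may want the effect net of uterotonics. That is a different estimand. It needs assumptions about common causes of uterotonic use and outcome that the article does not state.

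**Conclusion.** The point holds in limited form. As written, the rule permits adjustment for co-interventions given after treatment begins. Such adjustment departs from the total effect of assignment, most clearly for 24 h bleeding and contraction pain. It also does not match the centre-only primary model.

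A flat statement that the plan biases its estimates would go too far. Bias requires that EA alter co-intervention use, directly or through the outcome. There is none for co-interventions given before session 1, and none appeared in the bleeding simulations when EA had no effect. The illustrated attenuation of roughly 10% to 50% of a true bleeding effect rests wholly on assumed effects, triggers and noise. It shows direction, not the size to expect in this trial. The matter should be corrected, but it does not by itself undermine the primary comparison.

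**What to change.** Replace the last sentence of section 2.5.2.4 with: *Co-interventions will be recorded and tabulated by arm; models adjust only for centre and prespecified variables fixed before the first session (including uterotonics given before it); any analysis accounting for later co-interventions is labelled exploratory.* Carry the same wording into section 2.10 so that the two sections agree.

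The cost is one sentence in the protocol and the matching line in any analysis plan. The case report form must record the time of each co-intervention, so that use before and after the first session can be told apart. Sample size and trial conduct are otherwise unaffected.
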